#### Aim 2 and 3: prediction models

For the significantly changed outcomes of interest over time (change of coronal plane kinematics, prosthetic use, walking ability, HRQoL and prosthesis comfort) and for stump pain at follow-up, multivariate GEE [59, 61] will be used to examine which potential predictors are of added value in the prediction of these outcomes (Additional file 1). Potential predictors are age, BMI, time from primary amputation to inclusion, cause of amputation, level of amputation, length of the residual limb, baseline hip abductor strength, baseline prosthetic use, baseline mobility level, baseline walking ability and baseline prosthesis comfort. Baseline values of the outcomes of interest will also serve as potential predictors. The multivariate model will be reduced by manually removing predictors with a *p*-value of >0.15 based on the log-likelihood ratio test. Model performance will be assessed by the percentage of explained variance (R^2^) and C-statistics for continuous and categorical outcomes, respectively.

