An advantage of direct attachment to the bone, regardless of the used BAP method, is that the patient has a better ability to detect vibrotactile and pressure stimuli of the prosthetic limb compared to socket prosthesis users [22, 37, 38]. These stimuli are also known as osseoperception. Although BAP surgery has been performed for over 25 years only eight and generally small longitudinal studies [23, 25, 27–31, 39] assessed the level of function, activity and QoL outcomes of BAP compared to SP use. Various benefits have been found on body functions or structures (hereafter referred to as level of function), level of activity and HRQoL for BAP use compared to SP use [40, 41]. However, functional outcomes seem to be an underexposed part of BAP research to date. This is remarkable, because BAP surgery is an invasive intervention aimed to overcome problems in physical functioning in SP users with socket-related problems. In the SP population, complaints such as back pain may be the result of asymmetries in coronal plane gait kinematics and are possibly related to hip abductor strength deficiencies [20, 42], but have not been researched in the BAP population. Research on the level of satisfaction experienced by the patient with respect to their prosthesis is absent. Similarly, factors associated with outcomes regarding the levels of function, activity, HRQoL and satisfaction of the prosthesis after BAP surgery has not been researched. This study will address the above mentioned outcomes and follow, in part, the ICF classification [41]. The purpose of this manuscript is to detail the study protocol of an ongoing prospective 5-year longitudinal study with multiple follow-ups. The study focuses on patients with a lower extremity amputation who are fitted with a press-fit BAP and complete a standard rehabilitation programme. Through publishing this study protocol we aim to: a) increase the transparency of our data collection; b) prevent publication bias and selective reporting; c) prevent data dredging [43]. The study has four aims:

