Aim 1: to describe the change in the level of function, activity, HRQoL and satisfaction in patients with a lower extremity amputation after receiving a press-fit BAP at short-term (six-months and one-year), mid-term (two-years) and long-term (five-years) follow-up in comparison to baseline. We hypothesise that coronal plane kinematics symmetry, hip abductor strength, prosthetic use, mobility level, walking ability, HRQoL and prosthesis comfort will improve over time and that the frequency of back pain will decrease over time.

Aim 2: to examine potential predictors for the change of coronal plane kinematics, prosthetic use, walking ability, HRQoL and prosthesis comfort over time: outcomes that are the main reason why patients choose a BAP The potential predictors which will be included in the analysis are: demographic data, patient characteristics, baseline level of function, baseline level of activity and baseline level of satisfaction (Additional file 1).

Aim 3: to examine predictors for the level of stump pain at short-term, mid-term and long-term follow-up (Additional file 1). In our clinic we see that stump pain after BAP surgery negatively influences outcomes on the level of function, activity, HRQoL and satisfaction. However, we do not have insight in the level of stump pain at follow-up and knowledge concerning predictors for stump pain is absent.

Aim 4: to examine potential mechanisms for changes in back pain at short-term, mid-term and long-term follow-up. We hypothesise that an increase of coronal plane kinematics symmetry will be a possible determinant for a decrease in back pain (Fig. 1). We also hypothesise that stump pain will act as moderator and hip abductor strength will act as mediator.

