### Sample size

We will not draw a sample, but aim to include the entire population, which started in May 2014. We expect to have little non-responders as all assessments are part of usual care. This expectation is supported by the fact that we had no non-responders since the start of this study. Based on the average number of surgeries in the Netherlands during the year 2014 and 2015 we expect that 18 patients will be included each year [44]. For our first aim, investigating change over time, we will present the first interim analyses of this growing cohort when we have a minimum of 40 patients at the following time points: one-, two- and five-year follow-up. Press-fit BAP surgery started in the Netherlands in 2009. Between 2009 and 2014, 42 patients received a BAP. Thus at the time of our first interim analyses (mid of 2017) the total Dutch population with a minimum follow-up of one-year will include 82 patients [44]. Although, the sample size of 40 patients appears to be small, the study will have gathered longitudinal data (with a minimum follow-up of one-year) in 49% of the total Dutch population of patients with a press-fit BAP. We expect that this is sufficient to be able to generalise the results to the Dutch population eligible for a press-fit BAP. Of the patients included in this study to date, none have dropped out. We also do not anticipate any high drop-out rates for the remainder of the study as the assessments are part of usual care.

We will use the rule-of-thumb for prediction modelling with multiple factors and assume that we need ten cases per predictor [45]. The various continuous outcomes of interest have a different number of potential predictors (Additional file 1) ranging from three to seven variables. A minimum of 30 subjects are needed for prosthetic use, 40 subjects for HRQoL, 50 subjects for walking ability and prosthesis comfort, 60 subjects for coronal plane kinematics, and 70 subjects for stump pain. Based on these numbers we expect to complete the inclusion of patients for this study around May 2018.

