### Statistical analysis

All outcomes will be analysed non-stratified. Additionally, we will stratify for level of amputation and for baseline wheelchair-boundedness when applicable. The size of the subgroups will determine whether statistical tests will be used to analyse the outcomes of the subgroups, or if only descriptives will be presented. All analyses will be performed using SPSS v23 (SPSS Inc., Chicago, Illinois, United States). In all cases, two sided *p*-values <0.05 will be considered to be statistically significant.

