#### Aim 1: longitudinal statistics

Change over time in level of function, activity, HRQoL and satisfaction will be analysed for all continuous outcomes (coronal plane kinematics, hip abductor strength, prosthetic use, mobility level, walking ability, HRQL and prosthesis comfort) and for one categorical outcome (back pain). Generalised estimating equations (GEE) for repeated measurements with an exchangeable correlation structure will be used [59–61]. Back pain will be dichotomised for this analysis into ‘no back pain’ and ‘back pain’ (representing the classes ‘yes, with episodes’ and ‘yes, chronic (daily)’). Continuous outcomes (mean change) and the dichotomised outcome (odds ratio) will be presented with 95% confidence intervals.

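### Aim 2 prediction models are conditional on a significant change over time, although the aim and its sample sizes cover all five outcomes unconditionally

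*Protocol article*

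**What the plan says.** In the protocol article, the section on Aims 2 and 3 (prediction models) opens "For the significantly changed outcomes of interest over time (change of coronal plane kinematics, prosthetic use, walking ability, HRQoL and prosthesis comfort" and continues "and for stump pain at follow-up, multivariate GEE". The five Aim 2 outcomes therefore carry a significance condition. Stump pain (Aim 3) is joined separately and does not.

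The opening of the Statistical analysis section supplies the threshold: two-sided p-values below 0.05 "will be considered to be statistically significant". The Aim 1 section supplies the quantity tested: "Continuous outcomes (mean change) and the dichotomised outcome (odds ratio) will be presented with 95% confidence intervals", estimated by GEE.

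The Background states Aim 2 as "to examine potential predictors for the change of coronal plane kinematics, prosthetic use, walking ability, HRQoL and prosthesis comfort over time", with no condition. The Sample size section says the authors "assume that we need ten cases per predictor", with candidate predictors "ranging from three to seven variables", and gives a minimum number of subjects for each Aim 2 outcome, also without condition. The Background lists among the reasons for publishing the protocol the wish to "prevent publication bias and selective reporting".

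The article does not explain the condition or say what happens to an outcome that fails it.

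**The concern.** Aim 1 asks whether patients change on average. Aim 2 asks whether the amount of change differs between patients in a way that baseline factors can predict. These are different quantities: the first is the mean of the individual changes, and the second concerns their spread around that mean. An outcome with a small mean change may combine patients who gain with patients who lose, and a predictor is then particularly useful. Testing the mean first removes that outcome for a reason unrelated to predictability.

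Two things are at stake. Part of a named aim can go unanswered, although the Discussion wants the results to support realistic expectations and possibly new inclusion criteria for surgery. In addition, the set of prediction models that appears depends on Aim 1 p-values, which fits poorly with the stated purpose of the publication.

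**Working it through.** **1. The plan's own figures.** Minimum N = 10 × number of candidate predictors.
- Prosthetic use: 10 × 3 = 30
- HRQoL: 10 × 4 = 40
- Walking ability and prosthesis comfort: 10 × 5 = 50 each
- Coronal plane kinematics: 10 × 6 = 60
- Stump pain: 10 × 7 = 70

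All match the Sample size section. Expected accrual is 18 per year × 4 years (May 2014 to May 2018) = 72. The sizing thus provides for all five Aim 2 models, gated or not.

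**2. Inputs for the probability of being dropped.** From the document: two-sided alpha 0.05; n = 40 (minimum for the first interim analysis of Aim 1); n = 72 (expected total). Assumed, because the document gives neither an effect size nor an SD of change: d = true mean change ÷ SD of change, at 0.2, 0.3 and 0.5.

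**3. One paired contrast (baseline against one follow-up).** Power comes from the noncentral t distribution with n−1 degrees of freedom and noncentrality d√n. P(dropped) = 1 − power.

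| n | d | d√n | Power | Dropped |
|---|---|---|---|---|
| 40 | 0.2 | 1.265 | 0.235 | about 77% |
| 40 | 0.3 | 1.897 | 0.457 | 54% |
| 40 | 0.5 | 3.162 | 0.869 | 13% |
| 72 | 0.2 | 1.697 | 0.388 | 61% |
| 72 | 0.3 | 2.546 | 0.709 | 29% |
| 72 | 0.5 | 4.243 | 0.987 | 1% |

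At d = 0 the outcome is dropped 95% of the time by construction.

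**4. Any of four contrasts.** There are four follow-ups, and the text does not name the contrast that must be significant. Suppose any one suffices, with the same true change at each visit and an exchangeable correlation, so that changes from a shared baseline correlate 0.5. By simulation, the outcome is then dropped about 49%, 23% and 1% of the time at n = 40 for d = 0.2, 0.3 and 0.5, and about 30%, 6% and 0% at n = 72. At d = 0 it is about 85%.

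**5. Does the gate track predictability?** Take an artificial extreme: one baseline factor splits patients into equal halves, one gaining and one losing 0.5 residual SD. The factor explains 0.5² ÷ (1 + 0.5²) = 0.20 of the variance in change. In 20,000 simulated trials with a single contrast, the mean change was significant, so that the model would be fitted, in about 3%. The factor itself was significant in 87% at n = 40 and 99% at n = 72. If group membership is random rather than fixed at half and half, the gate opens in about 5%. The case shows that the gate and predictability can be unrelated. It does not forecast this cohort.

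**The case against.** **The gate may seldom bind.** Patients are selected for socket-related problems that limit prosthetic use, and improvement is hypothesised for all five outcomes. With large improvements nearly every outcome passes: at d = 0.5 the single contrast drops 13% at n = 40 and 1% at n = 72. This stands and limits the severity. It does not make the gate a valid screen.

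**The drop rates depend on the reading.** The plan uses GEE over repeated visits, not one paired t-test, and steps 3 and 4 differ widely. In addition, n = 40 is an Aim 1 interim figure. Walking ability and prosthesis comfort need 50 subjects and kinematics 60, so those three models would not be due at n = 40 in any case. This also stands, and the rates are illustrations only. That the qualifying contrast, and which of the two walking-ability measures must pass, are left open is itself a weakness of the gate.

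**The parenthesis may merely list outcomes expected to change.** Results were unknown when the article was written, so the natural reading is a condition on a future test. If no condition was meant, the same edit is needed.

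**Stronger readings that the document does not support.** A reader might infer that outcomes with mixed individual changes are never modelled. That is wrong: such an outcome is modelled whenever its mean change is significant. A reader might also infer concealed selective reporting. The rule is published in advance, and Aim 1 results are planned for all continuous outcomes, so a reader could see which ones failed. What remains is a disclosed but results-dependent set of models. Nor is Aim 3 affected, since stump pain is not gated.

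**Conclusion.** The point holds at moderate severity. The analysis section adds a significance condition that the statement of Aim 2 and the sample sizes do not contain, and a test of mean change does not tell whether change can be predicted between patients. Any Aim 2 outcome whose change misses p<0.05 goes unmodelled, however strong its predictors.

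How often that happens cannot be derived from the document. Over the assumed range d = 0.2 to 0.5, it runs from about 77% to 13% at n = 40 and from 61% to 1% at n = 72 for a single contrast. If any of four follow-up contrasts may qualify, it runs from about 49% to 1% and from 30% to 0%. The fault matters for small to moderate mean changes and hardly at all for large ones. The Aim 1 estimates, the sample sizes, the stump-pain model and the Aim 4 analysis do not depend on it.

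**What to change.** In the section on Aims 2 and 3, remove significant change as a condition. State that the prediction models will be fitted and reported for coronal plane kinematics, prosthetic use, walking ability, HRQoL, prosthesis comfort and stump pain, whatever the Aim 1 p-value. If both walking-ability measures are used, say so and model both.

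The cost is one sentence and at most a few extra models on data already collected. The stated minimum numbers (30 to 70) do not change and remain within the expected 72. Some of the added models may explain little variance, and that should be reported as a result.

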**Methods/design:**

A prospective 5-year longitudinal study with multiple follow-ups. All adults, between May 2014 and May 2018, with lower extremity amputation receiving a press-fit BAP are enrolled consecutively. Patients with socket-related problems and trauma, tumour resection or stable vascular disease as cause of primary amputation will be included. Exclusion criteria are severe cognitive or psychiatric disorders. Follow-ups are planned at six-months, one-, two- and five-years after BAP surgery. The main study outcomes follow, in part, the ICF classification: a) level of function defined as kinematics in coronal plane, hip abductor strength, prosthetic use, back pain and stump pain; b) level of activity defined as mobility level and walking ability; c) HRQoL; d) satisfaction defined as prosthesis comfort and global perceived effect. Changes over time for the continuous outcomes and the dichotomized outcome (back pain) will be analysed using generalised estimating equations (GEE). Multivariate GEE will be used to identify potential predictors for change of coronal plane kinematics, prosthetic use, walking ability, HRQoL, prosthesis comfort and for the level of post-operative stump pain. Finally, potential mechanisms for change in back pain frequency will be explored using coronal plane kinematics as a potential determinant, stump pain as moderator and hip abductor strength as mediator.

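### The Aim 2 and 3 models are fitted by GEE, but predictors are removed on a log-likelihood ratio test, which is not defined for GEE

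*Protocol article*

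**What the plan says.** In the protocol article, under Aim 2 and 3: prediction models, multivariate GEE "will be used to examine which potential predictors are of added value in the prediction of these outcomes". The abstract (Methods/design) agrees: "Multivariate GEE will be used to identify potential predictors for change of coronal plane kinematics". The paragraph on Aims 2 and 3 then gives the rule for reducing each model: a predictor is taken out manually if its p-value exceeds 0.15, "based on the log-likelihood ratio test. Model performance will be assessed by the percentage of explained variance". The models apply to stump pain at follow-up and to those Aim 2 outcomes that changed significantly over time.

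Three other places bear on this:

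- Aim 1: longitudinal statistics names the only working correlation in the article: "Generalised estimating equations (GEE) for repeated measurements with an exchangeable correlation structure will be used". None is given for Aims 2 and 3.
- Sample size sets the scale of the models at ten cases per predictor: "A minimum of 30 subjects are needed for prosthetic use, 40 subjects for HRQoL", and so on up to 70 for stump pain.
- The opening of Statistical analysis fixes the software: "All analyses will be performed using SPSS v23".

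The article mentions no mixed model, quasi-likelihood criterion, adjusted likelihood ratio test, Wald test or score test.

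**The concern.** GEE estimates regression coefficients from a mean model, a working correlation and a robust variance. It does not specify the joint distribution of a patient's repeated measurements. There is therefore no log-likelihood to difference between two nested models, and no chi-square reference for such a difference. The article states the model, the test and the threshold, and the test does not belong to the model. An analysis plan would have to change this sentence; it could not merely add detail to it.

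The sentence decides which predictors are reported for up to six outcomes (five under Aim 2, plus stump pain). If it cannot be followed literally, the choice of replacement falls to the time of analysis, and different replacements keep different predictors. That sits badly with the article's own reasons for publishing the protocol, which include preventing selective reporting and data dredging (Background).

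**Working it through.** **Inputs from the article.** Retention threshold 0.15 (Aim 2 and 3). Four follow-ups, at six months and one, two and five years (Study procedures and parameters). The short-term period has two of these, six months and one year (Background, Aim 1), and short-, mid- and long-term results are to appear in separate articles. Three to seven candidate predictors per outcome (Sample size).

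**Assumptions.** The article gives no within-patient correlation ρ; I use 0.3, 0.5 and 0.7. The candidates are taken as fixed within a patient. The list fits this, although BMI and residual-limb characteristics are also recorded at follow-up.

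**Step 1: the stated sizes.** 10 × 3, 4, 5, 6 and 7 predictors = 30, 40, 50, 60 and 70. These reproduce exactly and are not in dispute.

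**Step 2: between-patient predictor, working-independence likelihood substituted.** With m follow-ups, treating visits as independent understates the variance of a between-patient effect by a factor of 1 + (m − 1)ρ. The chi-square (1 df) value for p = 0.15 is 2.07, so the actual level is P(χ² > 2.07 / [1 + (m − 1)ρ]).

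| Follow-ups | Factor at ρ = 0.3 / 0.5 / 0.7 | Actual level |
|---|---|---|
| 4 | 1.9 / 2.5 / 3.1 | 0.30 / 0.36 / 0.41 |
| 2 | 1.3 / 1.5 / 1.7 | 0.21 / 0.24 / 0.27 |

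**Step 3: simulation at the planned sizes.** A null baseline predictor, Gaussian outcome, exchangeable correlation, complete visits and 4,000 replicates per setting (Monte Carlo standard error near 0.18 is √(0.18 × 0.82 / 4000) ≈ 0.006). Proportion retained at nominal 0.15 with 70 patients and 7 predictors:

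| Test | 4 follow-ups, ρ = 0.3 / 0.5 / 0.7 | 2 follow-ups, ρ = 0.3 / 0.5 / 0.7 |
|---|---|---|
| Independence-likelihood ratio | 0.30 / 0.38 / 0.43 | 0.23 / 0.26 / 0.30 |
| Generalised score | 0.17 / 0.18 / 0.18 | 0.17 / 0.17 / 0.18 |
| Robust Wald, uncorrected | 0.19 / 0.20 / 0.20 | 0.19 / 0.19 / 0.20 |
| Likelihood ratio from a full exchangeable Gaussian model | 0.17 / 0.18 / 0.18 | 0.18 / 0.17 / 0.18 |

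With 30 patients and 3 predictors the pattern is the same. The independence-likelihood test reaches 0.44 (4 follow-ups, ρ = 0.7), the uncorrected Wald test 0.21 to 0.23 and the score test 0.17 to 0.19.

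**Step 4: predictor-by-time term.** For a purely within-patient contrast the relevant factor is 1 − ρ, so independence overstates the variance. The actual level is P(χ² > 2.07 / (1 − ρ)). With 2.07 / 0.7, 0.5 and 0.3 = 2.96, 4.14 and 6.9, this gives about 0.09, 0.04 and 0.01.

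**The case against.** The strongest reply is that the figures describe an analysis the article does not specify. Nothing says that a working-independence likelihood will be used, and the one working correlation named is exchangeable. An analyst who finds that the rule cannot be run may turn to a test that GEE does have, and the inflation then largely disappears (0.17 to 0.20 at 70 patients). This stands: the size of the harm is conditional on the substitution.

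A reader might infer that the rule will keep far too many noise predictors throughout. The article does not support that. Aim 2 concerns change over time. Using the baseline value of the outcome as a predictor makes a main-effect reading plausible, and stump pain at follow-up fits it, but the article does not fix the parameterisation. With predictor-by-time terms the error runs the other way.

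A reader might also infer that no likelihood-ratio-type procedure exists for GEE. That is too strong. Adjusted working likelihood ratio tests and quasi-likelihood criteria exist; the article names none of them, and none is the ordinary log-likelihood ratio test.

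Nor does the sentence on explained variance add an error, since R² can be computed from fitted values for continuous outcomes.

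Finally, the cohort is single-arm, the authors claim only preliminary insight into associated factors (Discussion), and 0.15 is already a liberal threshold. This lowers the severity. It does not make the stated test applicable.

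**Conclusion.** Wrong as written, and should be fixed. The mismatch between GEE and the log-likelihood ratio test is on the face of the text and depends on no assumption.

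Its numerical effect does depend on assumptions: that the working-independence likelihood is substituted, and that ρ lies between 0.3 and 0.7. On those terms a null between-patient predictor is retained about 30% to 43% of the time with four follow-ups and about 23% to 30% with two (70 patients), against a nominal 15%. A predictor-by-time term is tested at an effective level of about 0.09 down to 0.01, so real predictors would be discarded too readily. The cut-off does not operate at 0.15 in either case.

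The consequence is confined to predictor selection for stump pain and for the Aim 2 outcomes that change significantly. The Aim 1 estimates and confidence intervals are untouched.

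**What to change.** Keep GEE. In the paragraph on Aims 2 and 3, delete the reference to the log-likelihood ratio test and state that predictors with p > 0.15 are removed on the generalised score test. A robust Wald test with a small-sample-corrected variance is an acceptable alternative; the correction is needed because the uncorrected version retained noise at 0.19 to 0.23 with 30 to 70 patients.

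Replacing GEE with a mixed model is not required. Its likelihood ratio test did no better in the simulation than the score test (both about 0.17 to 0.18 at 70 patients), and it would add a distributional assumption for outcomes on bounded scales (0–100 and 0–10).

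The cost is one phrase in the analysis text and a check that the named software offers the chosen test. No new data are needed. The change should be made before the prediction models are fitted.

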
In our clinic patients who choose a BAP do this for various reasons, including the expectation to increase their level of function, activity, HRQoL and satisfaction. However, to our knowledge no previous research has been done concerning predictors for outcomes on the level of function, activity, HRQoL or satisfaction. Due to the lack of current evidence, no individualised care can be provided. This causes uncertainty concerning the result of the actual health benefits that a patient is hoping for when choosing for a BAP. This study will be the first to address this topic.

The main inclusion criteria for BAPs in current practice is the presence of socket-related problems. By eliminating these problems, patients aim to overcome limitations in their physical functioning. However, a part of the BAP population suffers from stump pain as result of stoma-related problems, reactivating muscles and reuse of the hip joint for weight bearing [34, 40, 46]. Because stump pain after BAP surgery can also negatively influence physical functioning it is important to quantify the prevalence, the level of stump pain and identify potential predictors. Knowledge concerning these aspects may influence the content of the rehabilitation programme.

In summary, the psychometric properties of some of the chosen measurement instruments are absent and may influence the interpretation of these outcomes. This study is the first to examine coronal plane gait kinematics, hip abductor strength, prevalence of back pain, prevalence of stump pain and level of satisfaction in patients after BAP surgery. This study will provides preliminary insight in associated factors for clinically relevant outcome measures after press-fit BAP surgery. This important knowledge can help patients and professionals alike, to establish realistic expectations of the expected natural course after BAP surgery. In turn, this could potentially result in new inclusion criteria for BAP surgery in the future.

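### Predictors are selected at p>0.15 and judged by R² with no optimism correction named in about 72 patients; for Aim 2 that R² may also mix baseline coupling with what the other predictors add

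*Protocol article*

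**What the plan says.** The Protocol article, section Aim 2 and 3: prediction models, uses multivariate GEE for the Aim 2 outcomes that changed significantly over time and for stump pain at follow-up. Predictors with p>0.15 on a likelihood-ratio test are removed by hand. On the outcome's own starting value it says: "Baseline values of the outcomes of interest will also serve as potential predictors". On performance it says: "Model performance will be assessed by the percentage of explained variance", with C-statistics for categorical outcomes.

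The Sample size section sizes these models by a rule of thumb, "assume that we need ten cases per predictor", with candidates "ranging from three to seven variables". This gives "A minimum of 30 subjects are needed for prosthetic use, 40 subjects for HRQoL, 50 subjects for walking ability and prosthesis comfort". The kinematics model is set at 60 and the one for stump pain at 70. On recruitment: "we expect that 18 patients will be included each year". Study population gives the window as May 2014 to May 2018.

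The Background section defines Aim 2 as prediction of change and Aim 3 as prediction of the level of stump pain. Stump pain is assessed only after surgery. The Discussion expects the findings to inform patients' expectations and adds that "this could potentially result in new inclusion criteria for BAP surgery in the future".

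**The concern.** An R² computed in the patients whose data chose the predictors credits the model with chance fit. Elimination at a lenient threshold adds to this, because noise predictors that happen to look useful are kept with inflated coefficients. The problem is largest where there are few patients per candidate.

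A second issue is separate. If the response is follow-up minus baseline, the baseline is part of the response and correlates negatively with it even when no group of patients benefits more than another. The section asks which predictors add something. One R² that includes this coupling cannot answer that.

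At stake is how much confidence clinicians place in these models when they counsel patients or consider who should be offered surgery.

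**Working it through.** **1. The plan's own figures.** Ten per candidate predictor: 10 × 3, 4, 5, 6, 7 = 30, 40, 50, 60, 70. These match the stated minimums exactly.

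**2. Patients available.** 18 per year × 4 years = 72. The largest model needs 70, so two patients remain and no separate validation sample is possible. With all 72 patients, the subjects per candidate are 72/3 = 24, 72/4 = 18, 72/5 = 14.4, 72/6 = 12 and 72/7 = 10.3.

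**3. Expected R² with no true predictor, before elimination.** For the full model it is p/(n-1): 7/69 = 0.101 with 7 candidates and 70 patients. With independent tests, the chance of keeping at least one noise predictor is 1 - 0.85^p: 0.68 for 7 candidates and 0.39 for 3.

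**4. R² after elimination.** Backward removal at p>0.15 by likelihood-ratio test was simulated in a Gaussian linear model with one time point and independent predictors, as a stand-in for the GEE (1,500 to 2,000 runs per setting). The documents give no true R², so 0 and 0.20 are assumptions. Apparent R² is compared with the R² of the same fitted model in new patients.

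| Patients | Candidates | Assumed true R² | Apparent R² | R² in new patients | Gap |
|---|---|---|---|---|---|
| 70 | 7 | 0 | 0.06 | -0.08 | 0.14 |
| 70 | 7 | 0.20 | 0.25 | 0.05 to 0.12 | 0.14 to 0.20 |
| 72 | 3 | 0 | 0.02 | -0.04 | 0.06 |
| 72 | 3 | 0.20 | 0.22 | 0.13 to 0.15 | 0.08 to 0.09 |
| 72 | 5 | 0.20 | 0.24 | 0.13 | 0.105 |

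In the 70-patient and 3-candidate rows with true R² 0.20, the better new-patient value has two candidates carrying the effect, and the worse has it spread evenly over all candidates. The 5-candidate row uses two. If a single candidate carries everything, the gap is somewhat smaller. A negative R² means that the model predicts new patients worse than the overall mean does. With no true predictor, 7 candidates and 70 patients, at least one noise predictor survived in about 70% of runs.

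**5. Baseline coupling (Aim 2, change-score response only).** Let the baseline and follow-up SDs be equal and their correlation be r. Then the covariance of baseline with change is (r - 1)σ² and the variance of change is 2(1 - r)σ². The squared correlation is (1 - r)²/[2(1 - r)] = (1 - r)/2. The documents give no r, so a range is shown.

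| r (assumed) | 0.3 | 0.5 | 0.7 | 0.8 | 0.9 |
|---|---|---|---|---|---|
| R² of change on baseline alone | 0.35 | 0.25 | 0.15 | 0.10 | 0.05 |

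With a follow-up to baseline SD ratio s, the formula is (rs - 1)²/(1 + s² - 2rs). This gives 0.51 to 0.60 for s = 0.7 and 0.00 to 0.20 for s = 1.3 over the same range of r, so the result is sensitive to s. With the baseline plus pure-noise candidates, ten patients per candidate and r of 0.5 to 0.7, elimination reported R² of 0.20 to 0.30 although no other predictor had any effect.

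**The case against.** The strongest objection is that the article nowhere says that R² will be computed in the development data, and it does not exclude an optimism correction. A journal article condenses a fuller plan, and internal validation is often described elsewhere. This stands as a limit on the wording. A reader might infer that the plan rejects correction, and the text does not support that. What it does fix is the selection rule, the performance measure and a cohort size that rules out a hold-out sample. Followed as written, these give an optimistic figure.

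Other stronger readings also fail:

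- *The models will be fitted in as few as 30 patients.* The 30 to 70 are minimums and about 72 patients are expected. For the 3-candidate model the gap is about 0.20 at 30 patients but 0.08 to 0.09 at 72. One caution remains: kinematics is recorded only in unaided walkers, so that model may have fewer than 72.
- *Regression to the mean inflates R² through overfitting.* The share (1 - r)/2 recurs in new patients. It arises only with a change-score response, and the section does not say whether the response is change or the follow-up value. It cannot touch stump pain, which has no preoperative measurement, so the 70-patient, 7-candidate example shows overfitting alone.
- *Dropping the baseline will often leave the other predictors unadjusted.* In the simulations with r of 0.5 to 0.7, the baseline was kept in 80% to more than 99% of runs.
- *Multi-category predictors break the ten-per-predictor rule.* Which models contain cause or level of amputation is set out in Additional file 1, which is not shown, and their coding is not given in the article.
- *Expected false retentions can be counted over all candidate terms.* That treats every term as null, including each outcome's own baseline, and assumes that all outcomes are modelled, although Aim 2 outcomes enter only if they changed significantly.

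The article is also modest about use. It speaks of preliminary insight and derives no selection rule from the models.

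**Conclusion.** The point holds in two separate parts.

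First, R² after elimination at p>0.15 in about 72 patients, without correction, will overstate performance in new patients. With an assumed true R² of 0.20 and 72 patients, the overstatement is roughly 0.08 with 3 candidates to 0.20 with 7. With no true predictor, 7 candidates and 70 patients, it is about 0.14. These sizes rest on the assumed true R², on independent predictors and on one time point standing in for repeated measures. The direction does not depend on the exact values. A C-statistic would be optimistic for the same reason, but its size was not worked out.

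Second, for Aim 2 outcomes analysed as change scores, listing the own baseline as one removable candidate lets coupling of 0.05 to 0.35 (equal SDs, assumed r of 0.9 to 0.3) pass as explained variance. Including the baseline is not an error. The weakness is that its share is not separated from that of the other predictors.

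This should be changed, but it does not invalidate the study.

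**What to change.** 1. Draw bootstrap samples of patients, keeping all visits of a patient together, and repeat the whole elimination in each. Report optimism-corrected R² or C-statistics for the reduced model, beside the full model without elimination.
2. For the Aim 2 outcomes, state the response explicitly. Use the follow-up values as the response (follow-up visits only), always keep the outcome's own baseline in the model, do not interpret it as a predictor of change, and report the R² gained beyond baseline.
3. Stump pain needs only step 1.

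The cost is a little more computing, a few sentences in the analysis section and lower reported R² values. No new patients or measurements are needed.
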